**Methods:**

This is a crossover trial targeting 40 men and women between 50 and 90 years of age with either mild or moderate symmetric sensorineural hearing loss. Consented, willing participants will be recruited from either an independent living accommodation or via a community database to undergo a 6-month intensive face-to-face auditory training program (active control). Participants will be assigned in random order to receive hearing aid (intervention) for either the first 3 or last 3 months of the 6-month auditory training program. Each participant will be tested at baseline, 3, and 6 months using a neuropsychological battery of computer-based cognitive assessments, together with a depression symptom instrument and a social interaction measure. The primary outcome will be cognitive performance with regard to spatial working memory. Secondary outcome measures include other cognition performance measures, depressive symptoms, social interaction, and hearing satisfaction.

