Studies have investigated the effects of auditory training with laptops and computers, such as with the Listening and Communication Enhancement (LACE) software, on generalization to speech perception, self-report of communication difficulties, and cognition [27,28,33]. The results of these studies have often demonstrated the efficacy of auditory training, despite the computerized method of auditory training perhaps resulting in lower compliance with training protocols [32]. In addition, Saunders et al [35] found that LACE training did not result in improved outcomes over a standard-care hearing aid intervention on its own. Furthermore, according to research studies [36,37], there are still a large number of outstanding questions on the benefits of auditory training, such as which aspects of auditory training protocols contribute to learning, how auditory training generalizes to benefits in everyday communication, how individual characteristics interact with training outcomes to identify candidacy for auditory training, and the identification of outcome measures that are appropriate and sufficiently sensitive.

Research has shown that hearing aid devices alone do not always adequately compensate for sensory losses despite significant technological advances in digital technology [38]. Therefore, the focus of intervention will consider face-to-face auditory training in conjunction with a hearing aid device, whereas the comparator (control) group will consider individualized face-to-face auditory training on its own.

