## Methods

### Trial Design

This study has a randomized crossover trial design. It attained ethics approval on July 22, 2016 (Swinburne’s Human Research Ethics Committee protocol number SHR Project 2016/159).

All participants will undergo an individualized face-to-face auditory training program for a period of 6 months and will be randomly allocated to one of the following groups:

Participants who will be fitted with hearing aids only for the first 3 months of the auditory training program—*Group A.*Participants who will be fitted with hearing aids only for the last 3 months of the auditory training program—*Group B.*

Participants will be tested at baseline, and at 3 and 6 months in terms of cognition, depressive symptoms, social interaction, and hearing satisfaction.

A crossover design is chosen to allow each participant to serve as their own control [39]. Group A participants will have the option to withdraw from the study after 3 months if they decide to purchase hearing aids immediately. Similarly, group B participants will also have the option of withdrawing from the study at any time. As all participants will receive auditory training for the entire duration of the study to address their hearing loss, participants will benefit from the study even when the hearing aid intervention is not in place.

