#### Auditory Training

Historically, auditory training has been provided in a face-to-face setting that centered on a range of auditory skills, including detection, discrimination, identification, and comprehension. Training often incorporated both drill-like activities, described as analytic therapy activities, and paragraph comprehension activities, which were synthetic in nature. For both activities, the auditory skills that were trained used various stimuli such as syllables, words, phrases, sentences, and continuous discourse [38].

All participants enrolled into the study will undergo weekly individualized face-to-face auditory training for a period of 6 months. Over the 6-month period, each participant will participate in two 12-week individualized speech tracking programs. Participants living in supported independent living accommodation will attend their auditory training sessions at their place of residence, once per week for the 6-month period. Participants living independently in the community will attend their auditory training sessions once per week at Swinburne University of Technology. Each auditory training session will last for approximately 15 min.

The type of counseling intervention that will be provided to participants is called Continuous Discourse Speech Tracking [44]. A key aspect of this approach is that the training will involve interaction (a vital component of real-life communication) between the researcher and the participants. In this process, the researcher will articulate a sentence or phrase in a novel or short story, and the task of the participant will be to repeat back verbatim the sentence or phrase. If the repetition is correct, the researcher will articulate the next phrase or sentence. If the repetition is incorrect, the researcher will repeat the phrase or sentence, or a portion of it, or may use other repair strategies, until the sentence or phrase is correctly repeated in its entirety. The procedure will be timed for 15 min and scored in number of words per minute transmitted. Tracking rate will be calculated as the number of words correctly repeated divided by the time elapsed.

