##### Blamey Saunders Speech Perception Test

A Web-based Speech Perception Test (SPT) will be used in addition to the standard audiogram for the purpose of measuring hearing loss. SPT is a monosyllabic word test used to characterize the form and degree of hearing loss [23]. There will be 5 SPT evaluations altogether: SPT will be performed without hearing aids at baseline, after 3 months, and then at 6 months for all participants included in the trial. It will also be performed with hearing aids immediately after participants are fitted with hearing aids for the first time and at the end of 3 months of auditory training while wearing a hearing aid.

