### Statistical Analysis

The following statistical analyses will be performed:

Baseline comparison of the 2 groups in terms of demographics, cognition, depression, social interaction, hearing loss, and hearing satisfaction by reporting descriptive statistics of each group as randomized, and an effect size of the difference using Cohen's d.Comparison of the 2 groups in terms of changes in cognition, depression, and social interaction from baseline to 3 months and 6 months, using a per protocol approach for the crossover analysis [39] and an intention-to-treat, multilevel model analysis [56]. These methods will be used to estimate any carryover effects [57].Analysis of SPT results with and without hearing aids as a measure of the efficacy of hearing aids and auditory training with and without hearing aids using multilevel models and again allowing for carryover effects.Analysis of the speech tracking rates from the two 12-week programs of speech tracking using a learning model as described by Blamey and Alcantara [25]. This analysis will yield learning and forgetting rates with and without hearing aids. These learning and forgetting rates are valid measures of cognitive processes that are likely to be affected by the use of hearing aids. These data will also be analyzed using multilevel models again allowing for carryover effects.Analysis of the aided and unaided scores from APHAB will be used to assess how the benefit of hearing aids differed between groups and over degree of hearing impairment (mild/moderate hearing loss).

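### The SPT item claims to measure the efficacy of auditory training, but everyone trains throughout, so only what hearing aids add can be estimated

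*Protocol article*

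**What the plan says.** The third item under Statistical Analysis reads "Analysis of SPT results with and without hearing aids as a measure of the efficacy of hearing aids and auditory training", and the sentence continues: "auditory training with and without hearing aids using multilevel models and again allowing for carryover effects". Its object is therefore the efficacy of hearing aids and also of training, both with aids and without them.

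The design sections describe training as common to all. Trial Design: "All participants will undergo an individualized face-to-face auditory training program for a period of 6 months". Auditory Training: "All participants enrolled into the study will undergo weekly individualized face-to-face auditory training for a period of 6 months". The abstract's Methods paragraph gives what is randomised: "Participants will be assigned in random order to receive hearing aid (intervention) for either the first 3 or last 3 months". Background and Rationale gives training its role: "the comparator (control) group will consider individualized face-to-face auditory training on its own".

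The section on the Speech Perception Test (SPT) sets the schedule: "There will be 5 SPT evaluations altogether". Of these, three are unaided ("SPT will be performed without hearing aids at baseline, after 3 months, and then at 6 months for all participants included in the trial"). Two are aided: one at first fitting and one at the end of the 3 aided months.

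**The concern.** A statement about the efficacy of training needs a comparison with no training. The trial has no untrained group, no untrained period and no run-in. A rise in unaided SPT over 0, 3 and 6 months is a before-after change that also contains time and the effect of repeated testing. A rise in aided SPT from fitting to the end of the aided period contains these and, in addition, getting used to the aids.

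At stake is the conclusion drawn from this item. As worded, it leaves room to present an uncontrolled change as evidence from a randomised trial that training works.

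**Working it through.** The plan states no figure for this item, so there is none to reproduce. The check is whether the effect can be identified from the schedule.

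**Inputs.** Training, aid order and test times come from Trial Design, Auditory Training and the SPT section. I assume that fitting follows the baseline tests in Group A and the 3-month tests in Group B. The article gives no order for the unaided and aided tests at the end of the aided period. The table takes unaided first.

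| Group | Test | Month | Months trained | Aided test | Months of aid use | Earlier SPTs |
|---|---|---|---|---|---|---|
| A | baseline | 0 | 0 | no | 0 | 0 |
| A | fitting | 0 | 0 | yes | 0 | 1 |
| A | 3 months | 3 | 3 | no | 3 | 2 |
| A | 3 months | 3 | 3 | yes | 3 | 3 |
| A | 6 months | 6 | 6 | no | 3 | 4 |
| B | baseline | 0 | 0 | no | 0 | 0 |
| B | 3 months | 3 | 3 | no | 0 | 1 |
| B | fitting | 3 | 3 | yes | 0 | 2 |
| B | 6 months | 6 | 6 | no | 3 | 3 |
| B | 6 months | 6 | 6 | yes | 3 | 4 |

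**Training against time.** The month and training columns are identical in all ten rows, so their correlation is 1.00. Start with intercept, group, aided test and aid use:

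- adding time as categories plus training gives rank 6 of 7 columns, and training is not estimable;
- adding linear time plus training gives rank 5 of 6, and training is not estimable;
- adding categorical time, training and earlier SPTs gives rank 7 of 8, and training is still not estimable.

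In the first of these models the aided-test effect and the aid-use effect are estimable. In the plain two-period layout training is a constant: rank 4 of 5, with the aid effect estimable and training not. As a check on the cause, adding a hypothetical untrained group gives full rank, 8 of 8, and training becomes estimable.

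**Training against repeat testing.** From the table, the sum of cross-products is 90 − 10 × 3 × 2 = 30. The sums of squares are 54 (months trained) and 20 (earlier SPTs). The correlation is 30 / √(54 × 20) = 0.91, which is strong but not exact. If time is assumed to have no effect, training becomes estimable, but only alongside this correlation.

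**Unaided change to 3 months.**

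- Group B: training + time + one earlier test.
- Group A: training + time + two earlier tests + 3 months of aid use.
- A minus B: aid use + one extra earlier test.

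Training and time cancel. What remains is the effect of aids plus one step of practice.

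**Can the model carry practice as well?** This depends on the order within the visit that ends the aided period. If the unaided test always comes first, every row of the table satisfies

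earlier SPTs = aided test + [month 3] + 2 × [month 6] + [visit ending the aided period] + 2 × [Group A at month 6].

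The last indicator is a free carryover term. A model with group, aided test, current aid period, free carryover, time and a linear count of earlier SPTs then has rank 7 of 8, and the aid effects are lost. If the aided test comes first at that visit, the same model has rank 8 of 8. If the aid effect is assumed to persist in full after the aids are returned (the months-of-aid-use column), the model with earlier SPTs has full rank, 7 of 7, under either order.

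**The case against.** The strongest reply is that the whole sentence can be read narrowly, as training with aids against training without aids. That is the randomised crossover contrast, it is estimable subject to carryover, and it fits the rest of the article. Both hypotheses in Study Objective compare aids plus training with training alone, and the Discussion says the design will show whether aids bring added benefit. This reading is fair. But the contrast measures what aids add and not whether training works, and the sentence names the efficacy of training. The Discussion calls the choice of comparator a possible limitation, but does not say that training's own effect cannot be estimated.

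Three stronger readings are tempting, and the article does not support them.

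- A reader might infer that the plan commits the authors to crediting any rise in scores to training. It does not: the item sets no before-after test and no rule of attribution. The fault is that its wording permits the claim.
- A reader might infer that training, time and practice are all completely aliased. Exact aliasing holds only between training and time.
- A reader might infer that practice is balanced because each participant has five SPTs. Only the totals are equal: before the 3-month visit Group A has had two SPTs and Group B one.

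It is also fair to say that SPT is not among the primary or secondary outcomes in Outcome Measures and is not in Table 1. The size of any practice effect is unknown, since the article does not say whether word lists are varied, which a full protocol may cover.

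**Conclusion.** The point holds in limited form. The stated aim for SPT goes beyond what the design can deliver: the efficacy of training, above all training without aids, is not identifiable, and no multilevel or carryover specification can supply the missing comparator. The aided-versus-unaided difference and the effect of aids added to training are estimable, subject to carryover and to the handling of repeat testing.

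This rests on training following the same weekly schedule in both groups, as the article states, and on time being allowed to affect scores. No share of an observed change can be assigned to training without an outside assumption, so no numerical bias is given. The issue is confined to a supporting analysis. The primary outcome, the secondary outcomes, the hypotheses and the sample size are untouched.

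**What to change.** Restate the SPT item so that it estimates (i) the aided-minus-unaided difference and (ii) the effect of aids added to training, in the planned multilevel model with period, carryover and the number of earlier SPTs. The last term is needed because Group A has had one more SPT than Group B before the 3-month visit.

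State the order of aided and unaided tests at the visit ending the aided period. If unaided always came first, a free carryover term and a linear count of earlier SPTs cannot both be fitted. In that case, report the model with each in turn and say what each assumes. Difference (i) then also contains one step of practice.

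Report within-person SPT change descriptively, as change during training that is not separable from time and repeat testing, with no efficacy claim or test for training. Treat the aided change from fitting to the end of the aided period in the same way, adding that it includes getting used to the aids.

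The cost is the wording of one item and some model specification. No new data are needed, provided that test order was recorded. The trial gives up a training-efficacy conclusion in a supporting analysis. Recruitment is complete and analysis is under way, so the change should be made before the SPT results are interpreted.

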In aural rehabilitation, hearing aid use and auditory training strategies contribute to improving auditory abilities. The basic function of hearing aids is acoustic amplification of sound signals with the aim of restoring the audibility of sounds, thus helping to improve speech perception [18]. Studies have examined the effects of hearing aid use by older adults on a broad range of cognitive functions, such as information-processing speed, memory, and verbal fluency. Preliminary research evidence has suggested that hearing aids may improve the cognitive abilities, social, emotional, psychological, and physical well-being of people [18-21]. Some studies reporting the cognitive and psychological benefits of using hearing aids in elderly people have shown that the effects of hearing aid use are most distinctive in the early periods of use [6]. Despite the high prevalence of hearing loss in older adults, and the consequences for health outcomes, people are generally slow to acquire hearing aids [22]. Less than 25% of people who would benefit from hearing aids actually own them [23]. Existing research in this area, attempting to describe the effects of hearing aids on cognition, often assessed global mental status rather than cognitive performance and often examined only a single measure of hearing [6,19,24], thus limiting the insights gained. These studies also lack data on the duration of hearing impairment and loosely define hearing aid use as the self-reported use of a hearing aid in either or both ears, thus making it unclear about how hearing loss may affect performance on measures of cognition.

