Auditory training is the use of instruction, drill, or practice, designed to increase the amount of information that hearing contributes to a person’s total perception [25]. For example, a person with a hearing impairment who is fitted with a new hearing aid may benefit from instruction and practice in recognizing sounds through the aid. Research has shown that new hearing aid users show greater benefit from auditory training than experienced hearing aid users [26]. Auditory training also shares processes in common with cognitive training for improving working memory, attention, and communication. Studies have shown that auditory training can produce prolonged cognitive performance improvements [27,28] and improve speech understanding [29,30]. Other studies have shown that the benefits of training for people with hearing loss in terms of improved speech understanding are best achieved if an integrated auditory-cognitive training approach is adopted [31].

Although the concept of auditory training is not new, its popularity has declined in recent years, and only a small proportion of audiologists (fewer than 10%) offer auditory training to patients with hearing impairment [32]. Also, limited auditory training effort has been directed toward adults with impaired hearing, and the focus of auditory training has historically been directed toward young children with profound or severe to profound hearing loss [33,34].

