This program is adopted for this sample population because training materials could be tailored to the personal interests of participants. The materials chosen for the speech tracking program will consist of short stories, which will be long enough to last for a full 12-week program. A new story will be started at the beginning of each 12-week program.

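### Speech-tracking learning and forgetting rates are declared cognitive measures, but an aided-unaided difference in them could arise from hearing alone

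*Protocol article*

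**What the plan says.** The fourth item under Statistical Analysis fits a cited learning model to the speech-tracking data from the two 12-week programs. On the result it says: "This analysis will yield learning and forgetting rates with and without hearing aids". It then gives the interpretation without qualification: "These learning and forgetting rates are valid measures of cognitive processes that are likely to be affected by the use of hearing aids". The only adjustment named is for carryover: "These data will also be analyzed using multilevel models again allowing for carryover effects".

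The data behind these rates are defined under Auditory Training. The researcher speaks a phrase, and "the task of the participant will be to repeat back verbatim the sentence or phrase"; a wrong answer leads to repetition or another repair strategy until the phrase is right. The score is a speed: "Tracking rate will be calculated as the number of words correctly repeated divided by the time elapsed".

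Background and Rationale describes what the aids do: "acoustic amplification of sound signals with the aim of restoring the audibility of sounds, thus helping to improve speech perception". It adds that a person with a newly fitted aid "may benefit from instruction and practice in recognizing sounds through the aid". Eligibility Criteria admits only people who have never worn aids.

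Outcome Measures names SUCCAB spatial working memory as primary and the other SUCCAB tests as secondary cognition measures. Tracking rates appear in neither list.

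**The concern.** The aid acts directly on how well the test material is heard. A misheard word costs time through repetition, so audibility enters the tracking rate whatever happens to cognition. If audibility also alters the shape of the curve over 12 weeks, it enters the learning and forgetting rates.

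The crossover does not separate the two explanations. In both groups audibility switches on and off together with the treatment, so each participant's own control period differs in hearing as well as in any cognitive effect. A carryover term deals with effects that persist after the aid is removed, not with effects of the aid while it is worn.

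The first hypothesis is worded for cognition in general and names no instrument. The Discussion concedes that participants with high baseline scores may show no cognitive improvement. If SUCCAB shows little, the quoted sentence leaves a second result at hand, already labelled cognitive, that hearing alone could produce.

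**Working it through.** The plan attaches no figure to this analysis, so there is none to reproduce. The question is whether a difference in learning rate can appear when true learning is identical and only audibility differs.

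**Inputs.** From the protocol: weekly sessions in 12-week programs, a words-per-minute score, and aided and unaided programs compared. Assumed, because the documents give no tracking values: an unaided curve starting at 40 words/min with a potential gain of 20 and a learning constant of 0.15 per week. The audibility effects below are also assumed.

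**Unaided curve.** y(w) = 40 + 20 × (1 − exp(−0.15w)), w = 0 to 11. The least-squares slope is 1.42 words/min per week.

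**Aided curve, same learning, audibility changed:**

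| Audibility effect (assumed) | Aided curve | Change in slope |
|---|---|---|
| Constant additive gain of 4 or 8 words/min | y + 4, y + 8 | 0% |
| Constant proportional gain, k = 1.1, 1.2, 1.3 | k × y | +10%, +20%, +30% (1.56, 1.71, 1.85) |
| Benefit growing from 0 to 10% over the program | y × (1 + 0.10w/11) | about +36% |

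**Ceiling.** With a maximum of 80 words/min, y(w) = 80 / (1 + exp(−(s + 0.08w))). The slope is 1.51 at s = 0. Audibility shifts of s = 0.5, 1.0 and 1.5 give 1.29, 0.99 and 0.71, which are falls of about 15%, 34% and 53%.

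**Does a proportional scale cure it?** On the log scale a constant factor k drops out of the slope. A growing benefit does not. The unaided curve ends at 40 + 20 × (1 − exp(−1.65)) = 56.2, a log gain of ln(56.2/40) = 0.339. A benefit growing to 10% adds ln(1.10) = 0.095, and 0.095/0.339 = 28%.

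So only an audibility gain that is constant over the program, and additive on the scale of the fitted model, leaves the learning rate untouched. The protocol's own remark on practice with a new aid, together with its restriction to first-time users, makes a growing benefit plausible.

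**The case against.** Several points on the other side stand.

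- **Rate, not level.** The endpoint is a rate of change. A constant shift in level need not touch it, and a ceiling can reverse the bias. A reader might infer that better hearing would be counted as better cognition; the documents do not support so fixed a direction.
- **The learning model is not shown.** It may separate level from learning, and an article may leave that to the full protocol or SAP. The objection holds for level, but such separation would not by itself remove a trend from adapting to the aid.
- **The switch at 3 months.** A reader might infer that the loss of aids in Group A would be fitted as forgetting: for k = 1.1 to 1.3 the level falls by 1 − 1/k, or 9% to 23%. That needs one curve with a common level across the switch. Nothing in the article says so. The two programs coincide with aid status, and "A new story will be started at the beginning of each 12-week program".
- **Place in the hierarchy.** Tracking rates are not listed outcomes, and changes in cognition are analysed in a separate item. A reader might infer that the first hypothesis is to be tested on them; no section says this.
- **Cognitive load.** The Background names it among the possible links between hearing loss and cognition, so better audibility may be part of the supposed route. That makes a cognitive contribution possible but does not make it identifiable from this task.
- **SPT data.** Word perception is to be measured unaided at baseline, 3 and 6 months, and aided at first fitting and after 3 months of aided training. These data bear on the problem, but the article does not link them to the tracking analysis.

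What remains is that the sentence declares the rates valid for cognition without qualification, and the design cannot support that for an aided-unaided comparison.

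**Conclusion.** The point holds as a fault of stated interpretation. An aided-unaided difference in tracking, learning or forgetting rates cannot be attributed to cognition, because the aid changes the audibility on which the task depends and neither the crossover nor a carryover term separates the two.

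The direction and amount are unknown. The illustrated range of −53% to +36% in slope, with zero included, rests wholly on assumed values; it shows what is possible and estimates nothing about this trial. The conclusion itself needs only the protocol's descriptions of the task, the aid and the participants.

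The reach is limited. The primary comparison on SUCCAB spatial working memory and the secondary SUCCAB measures are not affected. The damage is confined to this supplementary analysis and any cognitive claim drawn from it.

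**What to change.** Replace the sentence on validity with wording such as:

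> Tracking, learning and forgetting rates are supplementary outcomes of speech tracking and training. Because hearing aids alter the audibility of the task, differences between aided and unaided periods do not count as evidence for the first hypothesis. Conclusions on cognition rest on SUCCAB, with spatial working memory primary and the other SUCCAB measures secondary.

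Add that the rates will be interpreted alongside the aided and unaided SPT scores already scheduled. The change in aided SPT from first fitting to the end of the aided period shows whether aided perception grew. Training runs over the same months, so this is context for the rates and not a clean correction.

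Giving each aid-status and program segment its own starting level in the tracking model is optional. It protects against a level shift at the switch but does not remove an adaptation trend, so it cannot replace the change of wording.

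The cost is an edit to the text and the loss of one supplementary cognitive claim. No new data are needed.
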